***9.2 Monitoring and record of adverse events***

9.2.1 In delivery ward, intermittent maternal vital sign monitoring (every 1-2 hours) will be performed.

9.2.2 Continuous maternal vital sign monitoring will be performed from the initiating of epidural labor analgesia to 30 minutes after the administration of loading dose.

9.2.3 Continuous external fetal heart rate monitoring and/or tocodynamometry will be performed as indicated.

9.2.4 Continuous maternal vital sign and external fetal heart rate monitoring will be performed during the second stage of labor.

***9.3 Diagnosis and management of predictable adverse events***

9.3.1 Bradycardia is defined as HR <60 beats per minute, and is managed with atropine 0.2-0.4 mg (i.v., repeat in 5-10 minutes if necessary).

9.3.2 Hypotension is defined as systolic blood pressure <90 mmHg or a decrease of >30% from baseline and is managed with fluid infusion and/or vasopressors.

9.3.3 Maternal hypoglycemia is defined as blood glucose <3.3 mmol/L [20] and is managed with oral or intravenous glucose.

9.3.4 Maternal hyperglycemia is defined as blood glucose >11.1 mmol/L [21]; insulin will be administered prudently when considered necessary.

9.3.5 Neonatal hypoglycemia is defined as blood glucose <2.6 mmol/L [22, 23], and will be treated with 5% glucose oral feeding (10-ml) [24].

9.3.6 Neonatal hyperglycemia is defined as blood glucose >7.0 mmol/L. In term newborns, hyperglycemia is generally regarded as part of stress response and not managed unless blood glucose >10 mmol/L [25]. Considering the harmful effects of insulin-induced hypoglycemia, infants with hyperglycemia will be managed with a wait-and-see strategy in all participating centers.

9.3.7 Maternal nausea and vomiting during cesarean delivery is managed with antiemetics, including dexamethasone, 5-HT3 receptor antagonists (tropisetron).

9.3.8 Pulmonary aspiration is defined as the inhalation of oropharyngeal or gastric contents into the respiratory tract. Initial treatment of a significant aspiration consists of oropharyngeal or endotracheal suctioning, administration of bronchodilators for bronchospasm, and supplemental O2. Bronchoscopy may be used as indicated. Mechanical ventilatory support with positive end-expiratory pressure may be necessary if hypoxemia is severe. Empirical antibiotics will be administrated when considered necessary. Other management including pulse oximetry monitoring and chest radiography will be performed according to routine practice [26].

9.3.9 For parturients with adverse events that are suspected to be related to the study beverage, healthcare team members should provide management as above and according to routine practice; they can discontinue study beverage administration if considered necessary and inform the investigators.

***9.4 Record***

9.4.1 Any adverse event should be documented, including occurrence, type/diagnosis, time of diagnosis, management, duration of persistence, and sequelae.

9.4.2 All types of adverse event which occur to parturients in the trial will be reported as soon as possible after research staff become aware of the event.

9.4.3 Any adverse event should be followed up until it is completely resolved, or therapy terminated.

**10. Severe adverse events**

***10.1 Definition***

A severe adverse event indicates any unpredictable medical events that lead to death, threat to life, prolonged length of stay in hospital, persistent disability or vital organ dysfunction, or other severe results. In the present study, severe adverse events are monitored from the initiating of epidural labor analgesia until 2 hours postpartum in the delivery room (before being transferred to the postpartum ward).

***10.2 Management and report***

10.2.1 In case of any severe adverse events, stop study beverage intake and start treatment immediately.

10.2.2 In case of any severe adverse events, apart from active treatment and rescue, inform the principal investigator and the Ethics Committee within 24 hours by telephone and in written report.

10.2.3 In case of study related death, immediately stop the clinical trial, report the event to the Ethics Committee as soon as possible, record in detail and carefully preserve the related documents.

10.2.4 Any severe adverse event must be followed up until it is completely resolved, or the treatment is terminated.

**11. Unmask of blindness**

11.1 After each trial patient’s study is completed and all data have been inputted into the database and checked without mistakes, the database will be blindly reviewed, and the analysis sets will be defined.

11.2 Unblinding will be performed after the database is locked. The database will be sent to a biostatistician for statistical analysis.

**12. Database management**

12.1 Original data will be recorded in the case report forms promptly and accurately. All recorded data will be kept confidentially.

12.2 The completed case report forms will be checked by a study coordinator who is authorized by the principal investigator. Amendment will be made when necessary.

12.3 After accomplishment of data entry and check using a study-specific REDCap database [27], all case report forms will be stored in sequence.

12.4 Data management and data monitoring will be inspected by the Clinical Research Ethics Committee of Peking University First Hospital.

**13. Statistical analysis**

***13.1 Analysis populations***

13.1.1 Intention-to-treat population

This population includes all patients who are randomized into the study and completed expected follow-up. Exclusion of participants will be performed in a minimal and reasonable way according to the intention-to-treat principle. All efficacy evaluations will be performed in the intention-to-treat population.

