***3.3 Criteria of drop-out***

3.3.1 Exit by participants themselves (i.e., withdraw consents).

3.3.2 Loss to follow-up.

3.3.3 Ordered to exit by the investigators (poor compliance, occurrence of severe complications, or occurrence of severe adverse events).

For drop-out cases, detailed reasons should be recorded. The primary therapeutic effects recorded in the last time will be regarded as the final results. The cases will be included in the intention-to-treat analysis. The Case Report Forms of these cases will be kept for future reference.

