***3.4 Criteria of elimination***

Included patients will be excluded if they meet any of the following criteria:

3.4.1 Withdraw consents before intervention.

3.4.2 Do not receive any designated oral beverage.

3.4.3 No assessment result of the primary outcome.

The causes of elimination should be explained. The case will be excluded from the intention-to-treat analysis. The case report forms will be preserved for reference.

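### The set called intention-to-treat drops randomised women for post-randomisation reasons, and sections 3.3, 3.4 and 13.1.1 disagree about who is in it

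*Protocol*

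**What the plan says.** Three places in the protocol decide who enters the primary analysis.

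- **Section 13.1.1** defines the ITT set: "This population includes all patients who are randomized into the study and completed expected follow-up". It adds a general promise, "Exclusion of participants will be performed in a minimal and reasonable way according to the intention-to-treat principle", and gives the set its role: "All efficacy evaluations will be performed in the intention-to-treat population".
- **Section 3.4** lists three grounds for elimination: withdrawal of consent before intervention (3.4.1), "3.4.2 Do not receive any designated oral beverage", and absence of a primary outcome result (3.4.3). The consequence is explicit: "The case will be excluded from the intention-to-treat analysis".
- **Section 3.3** lists as drop-outs women who withdraw consent (3.3.1), "Loss to follow-up" (3.3.2), and exit ordered by the investigators for poor compliance, severe complications or severe adverse events (3.3.3). For these, "The primary therapeutic effects recorded in the last time will be regarded as the final results", and "The cases will be included in the intention-to-treat analysis".

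Section 13.1.2 builds the per-protocol set from three conditions: study beverage ingested, no prohibited food, follow-up complete. Section 5.2 states that participants, healthcare providers and investigators are not masked. Section 6.3.2 leaves the caesarean decision to the attending staff.

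**The concern.** An ITT set keeps every randomised woman in her assigned arm, so that the groups compared are those that randomisation made alike. Here, receipt of the beverage, completion of follow-up and availability of the outcome all arise after allocation and after the arm is known. They can also be linked to the outcome: the drink is offered only during epidural analgesia and taken at will (section 6.2), so a woman who goes quickly to caesarean, or delivers quickly, may never receive it. If that link differs between arms, the primary relative risk is biased.

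Separately, the sections give opposite instructions for the same woman. Two analysts following the protocol could arrive at different denominators. In an open-label trial, that choice should not remain open until the analysis sets are defined at database review (section 11.1).

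**Working it through.** **1. The same woman under each section.**

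| Woman | 3.3 | 3.4 | 13.1.1 |
| --- | --- | --- | --- |
| Lost to follow-up | in (3.3.2) | out if no outcome (3.4.3) | out |
| Ordered to exit, follow-up incomplete | in (3.3.3) | out if no outcome (3.4.3) | out |
| Withdraws consent before intervention | in (3.3.1) | out (3.4.1) | out if follow-up incomplete |
| Received no beverage, delivery mode known | not addressed as such | out (3.4.2) | in if follow-up complete |

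Every row contains a conflict. In the last row, a woman whose outcome is known is discarded.

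**2. The last-value rule.** Mode of delivery occurs once. A woman who leaves before delivery has no earlier value to carry, so section 3.3 gives no usable instruction for the primary outcome.

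**3. The per-protocol set as a check.** Once section 3.4 is applied, the ITT set already requires receipt of the beverage and completed follow-up. The per-protocol set then adds little beyond the prohibited-food condition, so agreement between the two analyses would say little about the effect of the exclusions.

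**4. The protocol's own sample size (section 4.2).** Inputs: 8% and 12%, two-sided 0.05, 80% power, 1:1.

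- Unpooled formula: n per arm = (1.96 + 0.8416)² × (0.08×0.92 + 0.12×0.88) / 0.04² = 880 after rounding up, total 1760, as stated. The pooled-variance formula gives 882 per arm, 1764.
- Drop-out: 1760 / 0.90 = 1956, against 2000 planned.

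**5. How large the bias could be.** Assumptions that are not in the documents: no true effect, 12% caesarean in both arms, 1000 women per arm, a fraction d excluded from each arm, and caesarean rate c among those excluded. The analysed rate is (0.12 − d×c)/(1 − d).

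- d = 10%, c = 30% in the carbohydrate-rich arm: (0.12 − 0.030)/0.90 = 10.0%.
- d = 10%, c = 12% in the low-carbohydrate arm: (0.12 − 0.012)/0.90 = 12.0%.
- RR = 10.0/12.0 = 0.83; ln RR = −0.182. With 900 per arm, SE = √(0.90/90 + 0.88/108) = 0.135.
- Probability that the upper 95% limit falls below 1: Φ(0.182/0.135 − 1.96) = about 0.27. The opposite tail is negligible, so two-sided rejection is also about 27%.

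Other values of d and c, by the same formulas:

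| d per arm | c, carbohydrate-rich / low-carbohydrate | Analysed rates | RR | Two-sided rejection |
| --- | --- | --- | --- | --- |
| any | 12% / 12% | 12.0% / 12.0% | 1.00 | 5% |
| 10% | 30% / 30% | 10.0% / 10.0% | 1.00 | 5% |
| 2% | 30% / 12% | 11.6% / 12.0% | 0.97 | 5.7% |
| 5% | 30% / 12% | 11.1% / 12.0% | 0.92 | 9.9% |
| 10% | 30% / 12% | 10.0% / 12.0% | 0.83 | 27% |

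**6. Power with everyone kept.** At 8% against 12%, power is 84.7% with 1000 per arm and 80.8% with 900. If 5% of the carbohydrate-rich arm receive no drink and have the 12% rate, that arm's rate becomes 0.95×8% + 0.05×12% = 8.2%, and power with 1000 per arm is 80.6%. If 10% do, the rate is 8.4% and power is 75.8%.

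**The case against.** The best defence has four parts.

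- **Few women may be affected.** Delivery happens in hospital, and adverse-event monitoring ends 2 hours postpartum (section 9.1), so missing outcomes should be rare. The 10% in section 4.2 is a drop-out allowance. Section 3.3 keeps drop-outs in, so 10% describes exclusions only if 13.1.1 overrides 3.3. No figure is given for the exclusions in section 3.4. This stands, and it limits the likely size. It does not rescue 3.4.2, which removes women whose outcome is known.
- **The arm difference is assumed.** Early caesarean or rapid delivery before any drink would, under no effect, act alike in both arms and leave the RR at 1.00. This stands: the 27% needs unequal caesarean rates among the excluded, which nothing in the protocol shows.
- **Section 13.1.1 promises minimal and reasonable exclusion, and section 11.1 has the sets defined at a blind review.** Neither cancels the explicit exclusions. A blind review also cannot undo what unmasked people have already decided about drinking, staying or leaving.
- **The word in 3.4.2 is receive, whereas section 13.1.2 says ingested.** Section 3.4.2 may therefore mean that no drink was provided. On either reading the event follows randomisation.

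A reader might infer that women who exit before delivery are counted as not having had a caesarean. The protocol does not say so. With nothing recorded there is nothing to carry, 3.4.3 points to exclusion, and section 13.5 does not replace missing intrapartum data, among which section 7.2.1 lists mode of delivery. A reader might also infer that recorded volume and calories reveal the arm at the blind review. That is plausible, but water is free in both arms and section 11.1 does not say which fields are seen. The point does not depend on it.

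**Conclusion.** The point holds as a matter of definition. The primary efficacy set is not ITT, and the protocol contradicts itself on its membership. It should be corrected before the analysis sets are defined, because it governs the primary comparison in an open-label trial.

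The bias is possible, not demonstrated. It ranges from none, when exclusions are unrelated to outcome or related equally in both arms, to a false 2-point difference with about 27% two-sided rejection in the adverse case with 10% excluded. With 5% excluded, rejection is about 10%; with 2%, about 6%. These figures rest on the assumed 30% and 12% caesarean rates among excluded women.

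It would be tempting to say that the exclusions could manufacture the whole 4-point effect the trial seeks. The adverse case gives half of it. To reach 8% against 12% with 10% excluded, caesarean among the excluded in one arm would have to be (0.12 − 0.90×0.08)/0.10 = 48%; with 5% excluded, (0.12 − 0.95×0.08)/0.05 = 88%. The documents give no support for such rates.

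**What to change.** - **Section 13.1.1:** define ITT as all randomised women, analysed in the arm assigned, whether or not they received the beverage. Remove only women who withdraw consent to the use of their data. Delete the completed-follow-up condition.
- **Section 3.4:** delete 3.4.2 as a ground for leaving ITT, and align 3.4.1 and 3.4.3 with 3.3 and 13.1.1 so that each kind of case has one stated treatment.
- **Section 3.3:** replace the last-value rule with the actual mode of delivery from the hospital record, for every woman, including those who stop the intervention.
- **Section 13.1.2:** keep beverage receipt and completed follow-up as conditions for the per-protocol set only. That makes it a distinct comparison again.
- If the reduced set is wanted, call it modified ITT and make it secondary.

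The cost is wording, plus retrieval of delivery mode for the few women who leave early. Women who did not drink will dilute the effect slightly. No extra enrolment is needed while they are few: with 5% of the carbohydrate-rich arm unexposed, power with all 1000 per arm (80.6%) is about that of 900 per arm after a 10% loss (80.8%). If the share neared 10%, power would be about 76%, so it should be monitored.

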***4.2 Sample size calculation***

In a pilot trial of our own, the rate of cesarean delivery was 8% of parturients with carbohydrate drink and 12% of those with clear liquid drink. We assumed similar rates in the present study. With the significance level set at 0.05 (two-sided) and power set at 80%, the sample size required to detect difference was 1760 parturients. Considering a drop-out rate of about 10%, we plan to enroll 2000 parturients. Sample size calculation was performed with the Stata 10.0 software (Stata Corp. LP, College Station, TX, USA).

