**5. Randomization and blinding**

***5.1 Randomization principle***

5.1.1 A biostatistician, who is independent of data management and statistical analyses, generates random numbers in a 1:1 ratio with a block size of 4 using the SAS 9.2 software (SAS Institute, Cary, NC). Randomization is stratified according to the study centers.

5.1.2 Study beverages (carbohydrate-rich beverage and commercially available low-carbohydrate beverages) are provided according to the randomization results by an anesthesiologist who does not participate in the other part of the study.

5.1.3 The results of randomization are sealed in opaque, sequentially numbered envelopes and stored at the sites of investigation.

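### The protocol defines the intention-to-treat set in conflicting ways: drop-outs are in under 3.3, but 13.1.1 admits only women who finished follow-up, which leaves up to about 200 women in dispute

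*Protocol*

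**What the plan says.** Four parts of the protocol bear on who is analysed for cesarean delivery.

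- **Section 3.3** counts as drop-outs women who withdraw (3.3.1), are lost to follow-up (3.3.2) or are ordered out by investigators (3.3.3). It takes their last recorded result as final and states: "The cases will be included in the intention-to-treat analysis".
- **Section 3.4** lists women to be removed from the intention-to-treat analysis: withdrawal before the intervention (3.4.1), no study beverage received (3.4.2), and "3.4.3 No assessment result of the primary outcome".
- **Section 13.1.1** defines the intention-to-treat population: "This population includes all patients who are randomized into the study and completed expected follow-up". It adds that exclusions will be few and reasonable under the intention-to-treat principle, and it runs every efficacy evaluation in this set.
- **Section 13.1.2** also makes completion of follow-up the third condition for the per-protocol set.

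Section 4.2 gives the only figure for the size of the group: "Considering a drop-out rate of about 10%, we plan to enroll 2000 parturients".

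**The concern.** The same population has two membership rules. Section 3.3 includes a woman because she is a recorded drop-out. Section 13.1.1 leaves her out if she did not finish follow-up. Because 13.1.2 imposes the same completion condition, 13.1.1 carries a per-protocol criterion into the set meant to protect the randomised comparison.

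The primary test rests on this set. By 5.2, participants, care providers and investigators all know the allocation. A woman's decision to leave, or an investigator's decision to end her participation, may therefore depend on the arm and on how labor is going. Removing her after randomisation, when her mode of delivery is known, can bias the relative risk. The condition is also unnecessary for this endpoint: mode of delivery is an intrapartum variable (7.2.1) and is known before the glucose tests at birth (7.3) and the end of the 2-hour postpartum observation (6.3.4, 9.1).

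**Working it through.** **1. The plan's own sample size.** Inputs from 4.2 and 5.1.1: 8% versus 12%, two-sided 0.05, 80% power, 1:1 allocation.

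- Unpooled variance: n per arm = (1.960 + 0.842)² × (0.12×0.88 + 0.08×0.92) / 0.04² = 7.849 × 0.1792 / 0.0016 ≈ 879.1. Rounded up, this is 880 per arm, or 1760 in total, as stated.
- Pooled variance under the null: 882 per arm, or 1764.
- Drop-out allowance: 1760 / 0.9 ≈ 1956, which the plan rounds up to 2000.

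**2. Size of the group.** 0.10 × 2000 = 200 drop-outs, so about 2000 women are analysed if all of them count and about 1800 if none does.

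**3. Where the rules disagree.**

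| Woman | 3.3 | 3.4 | 13.1.1 |
| --- | --- | --- | --- |
| A. Ordered out for poor compliance, but followed to the end | in | not removed | in |
| B. Mode of delivery known; leaves before later assessments | in | not removed | out |
| C. Lost, mode of delivery not recorded | in | out (3.4.3) | out |

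A is not in dispute. B is a direct contradiction between 3.3 and 13.1.1. C is included by 3.3.2 and removed by both 3.4.3 and 13.1.1. The protocol does not divide the 10% among these types, so the number in dispute lies between 0 and about 200.

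**4. Could the choice of set change the conclusion?** Section 13.6.1.1 declares superiority when the upper 95% limit of the relative risk is below 1. The counts below are assumed, with 100 drop-outs per arm. The interval is RR × exp(±1.96 × √(1/a − 1/n₁ + 1/b − 1/n₂)).

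| Completers (carbohydrate-rich vs low) | Drop-out events | All randomised | RR (95% CI), all randomised |
| --- | --- | --- | --- |
| 75/900 vs 108/900 | 20 vs 12 | 95/1000 vs 120/1000 | 0.79 (0.61 to 1.02) |
| 75/900 vs 108/900 | 12 vs 12 | 87/1000 vs 120/1000 | 0.725 (0.558 to 0.942) |
| 72/900 vs 108/900 | 12 vs 12 | 84/1000 vs 120/1000 | 0.700 (0.537 to 0.912) |
| 72/900 vs 108/900 | 20 vs 12 | 92/1000 vs 120/1000 | 0.767 (0.593 to 0.991) |
| 72/900 vs 108/900 | 30 vs 12 | 102/1000 vs 120/1000 | 0.850 (0.663 to 1.090) |

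Among completers alone, 75/900 vs 108/900 gives 0.69 (0.52 to 0.92) and 72/900 vs 108/900 gives 0.667 (0.502 to 0.885). Both are superior. In the first and last rows the conclusion depends on which section is followed. In the other three it does not.

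**5. Power under each rule** (8% versus 12%, normal approximation): Φ[(0.04 − 1.96√(0.18/n)) / √(0.1792/n)].

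- n = 900 per arm: (0.04 − 0.02772) / 0.01411 = 0.870, power 80.8%.
- n = 1000 per arm: (0.04 − 0.02630) / 0.01339 = 1.024, power 84.7%.

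**The case against.** The other side has several fair points.

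- **Leaving the intervention is not the same as failing follow-up.** Section 13.1.2 lists beverage intake, prohibited food and follow-up separately. Section 10.2.4 requires follow-up of severe adverse events after the beverage is stopped. Follow-up is short, so real losses may be few. This stands. A reader might infer that all 200 women are in dispute, or that every woman ordered out disappears from the primary test. The text supports neither, because a drop-out who is followed to the end is in the set under both sections.
- **Section 13.1.1 promises few exclusions, and 11.1 settles the sets at a blinded review before database lock.** Both reduce the room for selective exclusion. Neither removes the contradiction. The promise does not readmit women who fail the definition, and a review cannot apply two opposite rules. The SAP, which is not at hand, may choose one, but the protocol would still state both.
- **Section 3.4.3 can be read as an exception to 3.3.** That could settle type C, but not type B.
- **The change of conclusion needs chosen counts.** This stands. With 72/900 among carbohydrate-rich completers, the plan's own 8%, 20 versus 12 drop-out events still leave the upper limit at 0.991. With 75/900 and equal drop-out events, the result also stays superior.
- **Power.** A reader might infer that counting drop-outs takes power below 80%. A figure of 76% does arise if every carbohydrate-rich drop-out keeps the 12% risk (0.9 × 8% + 0.1 × 12% = 8.4% versus 12%, 1000 per arm). That is an added assumption of full dilution, not a consequence of the membership rule. At half dilution (8.2%) power is about 81%.
- **Section 4.2.** A reader might take the 10% allowance as proof that drop-outs are meant to leave the analysis. It fits the removals in 3.4 equally well, so it does not settle the intention.

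**Conclusion.** The protocol is wrong as written. Sections 3.3 and 13.1.1 give incompatible rules for the primary analysis set, and 3.4.3 overlaps with 3.3.2. The dispute covers up to about 200 of 2000 women. That ceiling rests on the plan's assumed 10%, and the true number may be much smaller. The main harm is possible bias: under 13.1.1, women with a known mode of delivery can be dropped from an unmasked comparison for reasons related to arm or outcome. A different superiority conclusion is possible but needs a strong imbalance between arms among drop-outs, and the counts that show it are assumed. Power meets the stated 80% under either rule when the planned rates hold, so no power shortfall should be claimed. The conflict should still be resolved before analysis, because it governs the denominator of the primary outcome.

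**What to change.** - **13.1.1:** define the intention-to-treat set as all randomised women, analysed in the assigned arm, whether or not they completed the intervention or follow-up.
- **3.3:** for the primary outcome, replace the last-recorded-result rule with mode of delivery from the hospital birth record, where the woman's consent allows its use.
- **3.4:** reconcile all three criteria with the new definition. As they stand, 3.4.1 and 3.4.2 would still remove randomised women. Exclude only women whose delivery outcome cannot be obtained or used. Add a sensitivity analysis that gives those women the best and then the worst outcome, in opposite directions by arm.
- **13.1.2:** keep completion of follow-up as a condition here only.
- **SAP:** if one exists, it should carry the same definition.

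No change to the sample size or the power statement in 4.2 follows from this point.

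The cost is a wording amendment and a look-up of birth records for drop-outs. The effect estimate may be somewhat diluted, because women who left the intervention are counted in their assigned arm.
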